#### Handling of incomplete FI assessments

2.6.1.2 

(1). If a patient experiences an ICU disposition (death or discharge/transfer) within 7 days of ICU admission, the FI window spans ICU admission to the time of disposition. (2). If no prespecified gastrointestinal (GI) symptom is documented and the patient has an ICU disposition within 72 h of EN initiation such that FI cannot be fully ascertained, the primary analysis will classify the patient as no FI.

Adjusted FI (aFI) sensitivity definition. For the scenario described in rule (2) above, we prespecify an adjusted FI endpoint (aFI) for sensitivity analyses:

If any EN reduction is recorded, classify as FI

If no EN reduction is recorded, classify as no FI.

#### Secondary outcome definition and measures

2.6.2 

Achievement of nutritional targets: Receiving at least 80% of the estimated nutritional goals by day 7 after ICU admission(defined as energy intake ≥ 25 kcal/kg/day and protein intake ≥ 1.3 g/kg/day)28-day mortality: Assessed on day 28 after ICU admission90-day mortality: Assessed on day 90 after ICU admissionHealth-related quality of life (HRQoL) measured by SF-36 (Short Form-36 Health Survey): Assessed on days 28 and 90 after ICU admissionHealth-related quality of life measured by EQ-5D-5L (EuroQol 5 Dimensions 5 Levels): Assessed on days 28 and 90 after ICU admissionDiaphragm thickness: Measured on day 7 after ICU admissionQuadriceps muscle thickness: Measured on day 7 after ICU admissionRectus femoris cross-sectional area: Measured on day 7 after ICU admissionUpper limb muscle thickness: Measured on day 7 after ICU admissionNew infections in the ICU: Defined as infections newly acquired ≥ 48 hours after ICU admissionICU length of stayVentilator-free days: Ventilator-free days within 28 days in the ICU

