#### Duration of treatment and follow-up

2.6.4 

The study intervention will continue for 28 days following ICU admission, unless the patient is discharged from the ICU, discharged from the hospital, or dies earlier. All randomized patients will be followed for 90 days after ICU admission, unless death occurs first. If a patient remains hospitalized on day 90, follow-up will be conducted and outcomes will be recorded based on the patient’s status on day 90.

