#### Data analysis

2.7.1 

All statistical analyses will be conducted in accordance with a pre-specified statistical analysis plan. The primary analysis will follow the intention-to-treat (ITT) principle, with adjustment for clustering. The primary outcome (FI, binary) will be analyzed using a generalized linear mixed model (GLMM, logit link) with a random intercept for ICU/cluster and fixed effects for treatment and the pre-specified covariates (APACHE II score, AGI grade, primary diagnosis). To guard against model mis-specification and unequal cluster sizes, cluster-robust (sandwich) standard errors will be used for inference with between-cluster degrees of freedom; if convergence or small-sample issues arise, a wild cluster bootstrap-t procedure will be applied as a pre-specified fallback. Operationally, the full analysis set (FAS) will be used, defined as all randomized patients who have at least one valid post-randomization assessment of the primary outcome. The PPS, defined as patients who received protocolized EN for at least 48 h, will be used for sensitivity analyses.

Binary secondary outcomes (e.g., achievement of nutritional targets by day 7) will be analyzed analogously with GLMM (logit); continuous outcomes will use linear mixed models with a cluster random intercept and Kenward–Roger degrees-of-freedom adjustment. In addition, the EFI will be applied as a prespecified sensitivity analysis of the primary outcome to assess the robustness of the findings.

Continuous variables will be summarized as mean ± standard deviation if normally distributed, or as median and interquartile range (IQR, P25–P75) if not normally distributed. Between-group differences in continuous variables will be tested using the independent samples *t*-test for normally distributed data or the Mann–Whitney *U*-test for non-normally distributed data. Categorical variables will be compared using the Chi-square test.

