Sensitivity analyses will include: (i) an unadjusted GLMM (treatment + random intercept only); (ii) a covariate-enriched GLMM that adds baseline mechanical ventilation and sepsis (yes/no; protocol-defined) on top of the pre-specified covariates (APACHE II score, AGI grade, primary diagnosis); and (iii) aFI. All covariates are pre-specified and retained regardless of statistical significance. We will report adjusted odds ratios (95% CIs) for binary endpoints (with marginal risk differences via standardization as supportive estimates). The primary endpoint will be tested at two-sided α = 0.05 without multiplicity adjustment. For prespecified clinical secondary endpoints, we will control the false discovery rate at *q* = 0.05 using the Benjamini–Hochberg procedure (two-sided *p*-values from the specified models). Process outcomes (fidelity, exposure, contamination) are exploratory and will be summarized descriptively with 95% CIs; no hypothesis testing or multiplicity adjustment will be applied to these measures. All analyses will be performed using SAS software version 9.4^®^ (SAS Institute Inc., Cary, NC, United States).

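### As worded, ventilator-free days earn no credit after ICU discharge, and ICU stay in a linear model counts an early ICU death as a short stay

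*Protocol article*

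**What the plan says.** In the protocol article, section 2.6.2 (Secondary outcome definition and measures) lists "Ventilator-free days within 28 days in the ICU" and, by name only, ICU length of stay. Mortality is a separate secondary outcome there ("28-day mortality: Assessed on day 28 after ICU admission", and again at day 90) and is not combined with either.

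Section 2.7.1 (Data analysis) states that "continuous outcomes will use linear mixed models with a cluster random intercept and Kenward–Roger degrees-of-freedom adjustment". No exception is made for these two outcomes. The same section also says "Between-group differences in continuous variables will be tested using the independent samples" *t*-test, or the Mann–Whitney test when data are not normal. For the clinical secondary endpoints "we will control the false discovery rate at" *q* = 0.05, with p-values taken from the specified models.

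Death and discharge have an explicit rule only for feeding intolerance (FI), in section 2.6.1.2: "the FI window spans ICU admission to the time of disposition". Section 2.6.4 says "All randomized patients will be followed for 90 days after ICU admission, unless death occurs first", so observation does not end when the patient leaves the ICU.

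**The concern.** Ventilator-free days are meant to rise with recovery and to fall with prolonged ventilation or death. A count confined to the ICU breaks the first property, because each day by which a recovered patient leaves earlier removes a day of credit. An arm that gets patients out of the ICU faster would then look worse.

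ICU length of stay has a different problem. Death ends the stay, so an early death enters a mean-based model as a small value, and small values are read as favourable. An arm with more early deaths can show a shorter mean stay with no benefit to anyone.

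Both outcomes appear to belong to the family under false-discovery-rate control, so the stated model would supply the p-value for a formal claim.

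**Working it through.** **Plan's own figures.** The article gives no expected value, difference or standard deviation for either outcome, so there is nothing to reproduce for them. The sample size concerns FI only. It reproduces: 329 per arm for 0.5 against 0.375 at 90% power; design effect 1 + 24 × 0.10 = 3.4; 329 × 3.4 / 45 = 24.9, rounded to 25 per cluster; 25 × 45 × 2 = 2,250. It has no bearing on this point.

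**Step 1: score example patients.**
- ICU-only count = min(28, ICU days) − ventilated days.
- Plain count = 28 − ventilated days, with no rule for death.
- Conventional count = plain count, but 0 if dead by day 28.

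| Patient | ICU-only | Plain, no death rule | Death = 0 | ICU stay |
|---|---|---|---|---|
| Ventilated 3 d, discharged alive day 5 | 5 − 3 = 2 | 28 − 3 = 25 | 25 | 5 |
| Ventilated 3 d, in ICU to day 20, alive | 20 − 3 = 17 | 25 | 25 | 20 |
| Dies ventilated on day 3 | 3 − 3 = 0 | 28 − 3 = 25 | 0 | 3 |
| Extubated day 2, dies in ICU day 10 | 10 − 2 = 8 | 28 − 2 = 26 | 0 | 10 |

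On the ICU-only count, the patient who recovers and leaves first (2) ranks below the patient who dies on day 10 (8). On the plain count, the day-3 death (25) ties with both survivors. Only the last scoring orders all four sensibly.

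**Step 2: what happens to arm means.** This is an illustrative simulation with 400,000 patients per arm. Its assumptions are not in the documents: mean ventilation 6 days, mean ICU stay after extubation 5 days, deaths uniform over days 1 to 10, base mortality 10%, 20% or 30%.

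| Change in one arm | ICU-only | Plain | Death = 0 | ICU stay |
|---|---|---|---|---|
| 40% shorter ICU stay after extubation | −1.5 to −1.8 | about 0 | about 0 | −1.5 to −1.8 |
| 5 points more early death | about −0.2 | +0.11 | −1.1 | about −0.3 |

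In the first row, the same 1.5 to 1.8 days read as harm on ICU-only ventilator-free days and as benefit on ICU stay.

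**Step 3: ICU stay by hand.** With mortality m, mean stay = (1 − m) × S + m × D, where S and D are the mean stays of survivors and of deaths. Raising m by 0.05 changes the mean by −0.05 × (S − D). Assuming S = 12 and D = 6, this is −0.05 × 6 = −0.3 days. If S − D is 3 days it is −0.15; if 9 days, −0.45. The sign reverses if those who die stay longer than survivors.

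**Step 4: compare with sampling error.** Assume a standard deviation of 6 to 12 days and an intraclass correlation of 0.02 to 0.10, with 1,125 patients per arm and 25 per cluster. The design effect is 1 + 24 × 0.02 = 1.48 to 1 + 24 × 0.10 = 3.4. The standard error of the arm difference runs from 6 × √(2 × 1.48 / 1,125) = 0.31 to 12 × √(2 × 3.4 / 1,125) = 0.93 days. The 0.3-day artefact is at most about one standard error.

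**The case against.** The strongest reply is that this is a condensed article pointing to a statistical analysis plan that is not shown. How deaths are scored, and how ICU stay is handled in non-survivors, are details such a plan often holds. That stands: the absence of a death rule is not in itself a fault. What remains is printed text, namely the ICU wording and a linear model for continuous outcomes with no exception. An analysis plan that repaired these would depart from the article.

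A second reply is that the phrase is loose and may mean an ordinary 28-day count of ventilation recorded in the ICU. That is possible, and the scores of 2 and 8 depend on the literal reading. But the other reading also needs a value for death that the article does not give.

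Third, section 2.7.1 names neither outcome when it assigns the model, and it also mentions the Mann–Whitney test. The linear model is an inference, though the only model offered. Neither the *t*-test nor the Mann–Whitney test gives death a role.

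Fourth, the 0.3 days is assumed and small against its standard error, and mortality at days 28 and 90 would be reported alongside. This is correct and limits the weight of the ICU-stay part.

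A reader might infer something stronger: that both outcomes penalise early discharge and reward early death. The documents do not support that. Early live discharge counts as a gain for ICU stay. On the ICU-only count, more early death lowers mean ventilator-free days by about 0.2, even though a single later ICU death can outrank an early live discharge. Early death raises ventilator-free days only on the plain count without a death rule, and on that reading early discharge is not penalised.

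**Conclusion.** The point holds, separately for each outcome. As printed, ventilator-free days either withhold credit after ICU discharge, so that faster live discharge lowers the score, or, as a plain count, lack the value for death needed to keep a ventilated day-3 death from scoring 25. The first effect reached 1.5 to 1.8 days in the illustration, under assumed distributions and a 40% shorter stay after extubation. For ICU stay, excess early mortality can shorten the modelled mean, by about 0.3 days for 5 points of mortality under assumed mean stays of 12 and 6 days. That alone is unlikely to create a false claim, but it would bias the estimate in the favourable direction.

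The conclusion rests on the article's wording; an unseen analysis plan may already contain a death rule. Multiple imputation under missing at random (section 2.7.2) does not settle how an outcome cut short by death should be valued. Only secondary endpoints are affected. The primary outcome and the sample size are not.

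**What to change.** Define ventilator-free days as days alive and off invasive ventilation from day 1 to day 28 regardless of location, with 0 for death by day 28. Analyse them with an ordinal or rank-based method that accounts for ICU clustering, for example a proportional-odds model with an ICU random intercept.

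Analyse ICU stay as time to live ICU discharge, with death as a competing event and ICU-clustered standard errors. At the least, report stay by survival status next to mortality.

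The cost is a wording change and two model changes, made before the data are analysed. Most of the data are already planned: deaths are assessed at day 28 and follow-up runs to day 90. Ventilation after ICU discharge must be assumed absent, with that assumption stated, or asked at the day-28 contact. The effect measures become less direct than a mean difference in days; mean or median days can stay as description.

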#### Process measures

2.6.3 

To evaluate the implementation and adherence to nutritional strategies in both groups, the following process measures will be collected:

Time from ICU admission to initiation of feeding: to assess the timeliness of nutritional support initiation.Time from study enrollment to initiation of feeding: to evaluate the efficiency of implementing the assigned nutritional protocol after enrollment.Percentage of patients fed within 24 h of ICU admission: to assess compliance with early feeding recommendations.Mean daily energy delivered (kcal/kg/day): to quantify caloric intake and assess nutritional adequacy.Mean daily protein delivered (g/kg/day): to quantify protein intake throughout the ICU stay.Completeness of the feeding record forms in the intervention group: to assess fidelity to the mNEED protocol, reflecting whether nutritional interventions were implemented as per protocol.Daily caloric and protein intake in the control group: to determine whether the feeding pattern followed the progressive strategy recommended by the ESPEN guidelines (e.g., not exceeding 70% of energy expenditure in the first 3 days, and gradual advancement thereafter).Use of supplemental protein on day 4 after ICU admission (e.g., oral protein supplements or intravenous amino acids): to evaluate whether both groups followed guideline-recommended escalation of protein delivery, ensuring protein targets were progressively achieved.

#### Duration of treatment and follow-up

2.6.4 

The study intervention will continue for 28 days following ICU admission, unless the patient is discharged from the ICU, discharged from the hospital, or dies earlier. All randomized patients will be followed for 90 days after ICU admission, unless death occurs first. If a patient remains hospitalized on day 90, follow-up will be conducted and outcomes will be recorded based on the patient’s status on day 90.

#### Reasons for withdrawal/discontinuation

2.6.5 

If any serious adverse events related to the study occur during the trial, early withdrawal from the study will be permitted. In addition, if a patient or their legal representative requests withdrawal from the trial for any reason, early withdrawal will be allowed without affecting the patient’s future medical care from the investigators or study site. Efforts will be made to follow up all randomized patients to the extent permitted by their consent.

#### Intervention fidelity, contamination, and exposure

2.6.6 

Fidelity: Using the electronic feeding logs and CRFs, we will quantify protocol fidelity in the mNEED arm as the proportion of patients who completed every protocol-mandated EN dose adjustment at each scheduled assessment (per protocol rules). This will be summarized at patient and ICU (cluster) levels.

Contamination (control arm): Each control ICU will be contacted to confirm whether NOFI (the FI prediction model) was used to guide EN decisions. Any reported use of NOFI to guide EN in the control arm will be recorded as intervention contamination for that ICU.

Exposure metrics. To contextualize delivery of nutrition support, we will report: (i) time to EN initiation from ICU admission; and (ii) duration (days) under protocol-managed nutrition. These process measures are not clinical endpoints; they will be summarized descriptively and compared between arms.

### Data collection

2.7 

A secure web-based electronic data capture (EDC) system, provided by Unimed Scientific Inc. (Wuxi, China), will be used for data collection and storage. Each participating center will be assigned a single user account, and one designated staff member will be responsible for data entry. The trial management committee will oversee user authorization. Training on the use of the EDC system will be provided by the database vendor in collaboration with the coordinating center of the CCCNTG.

#### Data analysis

2.7.1 

All statistical analyses will be conducted in accordance with a pre-specified statistical analysis plan. The primary analysis will follow the intention-to-treat (ITT) principle, with adjustment for clustering. The primary outcome (FI, binary) will be analyzed using a generalized linear mixed model (GLMM, logit link) with a random intercept for ICU/cluster and fixed effects for treatment and the pre-specified covariates (APACHE II score, AGI grade, primary diagnosis). To guard against model mis-specification and unequal cluster sizes, cluster-robust (sandwich) standard errors will be used for inference with between-cluster degrees of freedom; if convergence or small-sample issues arise, a wild cluster bootstrap-t procedure will be applied as a pre-specified fallback. Operationally, the full analysis set (FAS) will be used, defined as all randomized patients who have at least one valid post-randomization assessment of the primary outcome. The PPS, defined as patients who received protocolized EN for at least 48 h, will be used for sensitivity analyses.

Binary secondary outcomes (e.g., achievement of nutritional targets by day 7) will be analyzed analogously with GLMM (logit); continuous outcomes will use linear mixed models with a cluster random intercept and Kenward–Roger degrees-of-freedom adjustment. In addition, the EFI will be applied as a prespecified sensitivity analysis of the primary outcome to assess the robustness of the findings.

Continuous variables will be summarized as mean ± standard deviation if normally distributed, or as median and interquartile range (IQR, P25–P75) if not normally distributed. Between-group differences in continuous variables will be tested using the independent samples *t*-test for normally distributed data or the Mann–Whitney *U*-test for non-normally distributed data. Categorical variables will be compared using the Chi-square test.

Sensitivity analyses will include: (i) an unadjusted GLMM (treatment + random intercept only); (ii) a covariate-enriched GLMM that adds baseline mechanical ventilation and sepsis (yes/no; protocol-defined) on top of the pre-specified covariates (APACHE II score, AGI grade, primary diagnosis); and (iii) aFI. All covariates are pre-specified and retained regardless of statistical significance. We will report adjusted odds ratios (95% CIs) for binary endpoints (with marginal risk differences via standardization as supportive estimates). The primary endpoint will be tested at two-sided α = 0.05 without multiplicity adjustment. For prespecified clinical secondary endpoints, we will control the false discovery rate at *q* = 0.05 using the Benjamini–Hochberg procedure (two-sided *p*-values from the specified models). Process outcomes (fidelity, exposure, contamination) are exploratory and will be summarized descriptively with 95% CIs; no hypothesis testing or multiplicity adjustment will be applied to these measures. All analyses will be performed using SAS software version 9.4^®^ (SAS Institute Inc., Cary, NC, United States).

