#### Randomization

2.4.1 

This study employed a multicenter, stratified block-randomized controlled trial with cluster allocation at the ICUs level. A total of 108 ICUs were enrolled, including 102 tertiary general hospital ICUs and 6 other-level ICUs, as of 15 June 2025. Stratified randomization was performed by first stratifying ICUs according to their level (tertiary general hospital/others), followed by generating block randomization sequences within each stratum using R software (version 4.4.1). Clusters were allocated in a 1:1 ratio to either the intervention group or control group. Finally, 54 ICUs were assigned to each group. Due to the nature of the intervention, a partial blinding approach was adopted: participating patients, center implementers, and outcome assessors were aware of group allocation, while members of the endpoint adjudication committee remained blinded to allocation status.

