This study also has important limitations. First, although FI was chosen as the primary outcome, its definition remains debated. Multiple diagnostic criteria exist; in this trial we adopted the widely accepted and relatively objective 2012 ESICM definition for FI, and applied the EFI definition as a prespecified sensitivity analysis. Despite this limitation, we consider FI the most suitable mediator between nutritional interventions and mortality. Second, center effects across nearly 100 ICUs are difficult to fully control. Although we stratified hospitals by level (secondary vs. tertiary) and performed randomization with a fixed seed, heterogeneity may still exist within the same level of hospitals—an inherent limitation of cluster-randomized designs, but also one that reflects the real-world variation in nutritional practice across China (19). Third, the feeding protocol in the control group was not entirely objective. Although based on the 2023 ESPEN guideline, interpretation of some aspects (e.g., initial feeding rate) remained subjective, which may have introduced variability in control group practices. Fourth, despite standardized ultrasound training delivered by CCUSG-certified instructors, operator-dependent variability could not be completely eliminated. Therefore, the change in muscle mass between day 1 and day 7 may be a more robust measure than the absolute value at day 7.

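### The stated primary GLMM, its two GLMM sensitivity variants and the binary secondary models leave out ICU level, the randomisation stratum; the effect is small and conservative

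*Protocol article*

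**What the plan says.** **Randomisation (section 2.4.1).** "Stratified randomization was performed by first stratifying ICUs according to their level (tertiary general hospital/others"). The allocation lists were then drawn up in blocks, separately for each level. The strata are very unequal: "A total of 108 ICUs were enrolled, including 102 tertiary general hospital ICUs and 6 other-level ICUs, as of 15 June 2025". Allocation was 1:1, and "Finally, 54 ICUs were assigned to each group".

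**Primary model (section 2.7.1).** A logit GLMM for FI with a random intercept for ICU and "fixed effects for treatment and the pre-specified covariates (APACHE II score, AGI grade, primary diagnosis"). Inference uses cluster-robust standard errors with between-cluster degrees of freedom, and a wild cluster bootstrap-t is the fallback if convergence or small-sample problems arise.

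**Sensitivity models (section 2.7.1).** One GLMM has treatment and the random intercept only. The other adds baseline ventilation and sepsis to the three primary covariates. The article states that every covariate is pre-specified and is kept whatever its significance.

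**Secondary models (section 2.7.1).** Binary outcomes "will be analyzed analogously with GLMM (logit"). For continuous outcomes the article names a linear mixed model with a cluster random intercept and Kenward–Roger degrees of freedom, and lists no fixed effects.

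**Limitations (section 3.1).** The stratum is described again, in other words: "Although we stratified hospitals by level (secondary vs. tertiary) and performed randomization with a fixed seed".

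**The concern.** Blocking within strata forces the arms to be alike on ICU level. The treatment estimate then varies less from one possible allocation to another than it would under simple cluster randomisation. A model without the stratum does not credit this. Any difference in FI between levels stays in the between-ICU variance and enters the standard error, although the design has already removed it from the treatment comparison. Cluster-robust errors do not correct this, because they too treat the ICUs as unrestricted draws. The three listed covariates are patient-level and do not encode hospital level.

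The article names its covariates, repeats the list and declares it pre-specified. For the primary model and its two variants, the omission is therefore a stated choice and not a detail left to the analysis plan. An analysis plan that added ICU level would depart from the published model.

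At stake are a little precision and a test that runs slightly below its nominal level.

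**Working it through.** **1. The plan's own figure.** Inputs from section 2.3: FI 0.50 against 0.375, two-sided alpha 0.05, power 90%, ICC 0.10, 45 clusters per group.

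- Individually randomised: 329 per arm.
- Cluster size m at k = 45 clusters: m = n(1 − ICC)/(k − n × ICC) = 329 × 0.9/(45 − 32.9) = 296.1/12.1 = 24.47, rounded up to 25.
- Design effect: 1 + 24 × 0.10 = 3.4. Total: 45 × 25 × 2 = 2,250. Power is 0.902.

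The stated sample size reproduces, and this point does not touch it.

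**2. Variance carried by the stratum.** Let q = 6/108 be the share of other-level ICUs and D the difference in FI between strata. The article gives no value for D, so 0.10, 0.20 and 0.30 are assumed.

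- Stratum variance: q(1 − q)D² = (6/108)(102/108)D² = 0.05247 D².
- With mean FI (0.50 + 0.375)/2 = 0.4375, p(1 − p) = 0.2461.
- Between-ICU variance: 0.10 × 0.2461 = 0.02461.
- Within-ICU variance of an ICU proportion: 0.90 × 0.2461/25 = 0.00886.
- Variance of an ICU proportion: 0.02461 + 0.00886 = 0.03347.
- Ratio of standard errors, stratum omitted over stratum included: 1/√(1 − stratum variance/0.03347).

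| D | Stratum variance | Share of ICU-proportion variance | SE ratio |
|---|---|---|---|
| 0.10 | 0.00052 | 1.6% | 1.008 |
| 0.20 | 0.00210 | 6.3% | 1.033 |
| 0.30 | 0.00472 | 14.1% | 1.079 |

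As a share of the between-ICU variance alone, the stratum accounts for 2.1%, 8.5% and 19.2%. Those figures look larger, but the SE ratio is what bears on inference.

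**3. Effect on the test.** Simulation with 40,000 replicates: 54 against 54 ICUs, 25 patients each, beta-binomial FI with ICC 0.10, the six other ICUs split 3:3, and ICU proportions analysed with and without the stratum.

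| D | Type I error, omitted | Type I error, included | Power, omitted | Power, included |
|---|---|---|---|---|
| 0 | 0.051 | 0.051 | 0.943 | 0.943 |
| 0.10 | 0.049 | 0.050 | 0.940 | 0.942 |
| 0.20 | 0.043 | 0.050 | 0.933 | 0.941 |
| 0.30 | 0.036 | 0.049 | 0.925 | 0.943 |

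The power loss is about 0.2, 0.8 and 1.8 points. The mean estimated effect is −0.125 either way, so the omission causes no bias under this split. The formula in step 2 gives similar type I errors (0.048, 0.043, 0.034) and losses of 0.2, 0.6 and 1.2 points. The two differ a little because the formula counts the stratum within the ICC of 0.10, whereas the simulation adds it on top.

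**4. Limits of the check.** It works on ICU proportions, not on the logit GLMM, and has no patient-level covariates. A 3:3 split fits the reported totals (51 + 3 = 54 per arm), but the article states neither the split nor the block size.

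**The case against.** The strongest case on the other side is that this hardly matters. The stratum holds 6 of 108 ICUs. The random intercept absorbs differences by level, the error is conservative, and even an assumed 30-point gap leaves simulated power at 0.925. Part of any such gap may also be explained by APACHE II, AGI grade and diagnosis, which the check ignores. All of this stands and sets the size of the point. It does not remove the point, because the omission is explicit and putting it right is nearly free.

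A reader might go further in three ways that the article does not support.

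- **That the analysis ignores the randomisation.** It does not. The ICU is the unit of randomisation, and the random intercept with between-cluster degrees of freedom respects it. Only the stratum term is missing.
- **That every secondary model omits the stratum.** For binary outcomes this follows from the reference back to the primary model. For continuous outcomes no fixed effects are listed at all. That is silence in a condensed article and may be settled in the analysis plan.
- **That two different stratifications were used.** Section 3.1 writes "Although we stratified hospitals by level (secondary vs. tertiary"), whereas section 2.4.1 contrasts tertiary general hospitals with others. A tertiary specialist hospital would fall on different sides of the two wordings, but the article does not say that one was enrolled. Section 2.2.3.1 admits only secondary and tertiary hospitals, and section 2.4.1 calls the six ICUs other-level, so both wordings may describe the same split.

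**Conclusion.** The point holds as a minor one. ICU level stratified the randomisation and is absent from the stated primary GLMM, from both GLMM sensitivity variants and, by reference, from the binary secondary models. The standard error is about 1%, 3% or 8% too large at assumed gaps of 10, 20 or 30 points between strata, with a power loss of about 0.2, 0.8 or 1.8 points and a type I error below 0.05. If FI does not differ by level, nothing is lost.

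These sizes rest on the assumed gaps, the assumed 3:3 split, 25 patients in each of the 108 ICUs, and an ICC of 0.10. If the six ICUs did not divide evenly, omitting the stratum would also leave a small imbalance uncorrected. It is not sized here, because the split is not given. Nothing in the article suggests that the trial's conclusion is at risk.

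**What to change.** - Add ICU level, coded exactly as in the randomisation list, as a fixed effect in the primary GLMM, the covariate-enriched GLMM and the binary secondary models. Carry it into the continuous secondary models when their fixed effects are written out.
- Leave the unadjusted GLMM as it is, or include the stratum and label that model as adjusted for stratum only.
- State the rule for non-convergence: if the model with the six-ICU stratum fails to converge, refit it without that term first, and only then use the wild cluster bootstrap-t fallback.
- Align the wording in section 3.1 with section 2.4.1, as a clarification, so that the coding of the variable is not in doubt.

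The cost is a line in the analysis plan, one between-cluster degree of freedom and one corrected phrase. The sample size does not change. The amendment should be dated before outcome data are unblinded, because a covariate added later to a list declared pre-specified would look post hoc.
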